### 2.4. Participant Retention Strategies

The research team will use a range of equitable and inclusive strategies to ensure participant retention and mitigate attrition throughout the study. Once participants have completed the intake process and are fully onboarded, they will be assigned to a treatment group and a therapist. Through the sessions, the research team, including the therapists, will work with participants to sustain their participation and address barriers to their participation as they emerge. Participants will receive reminders based on their contact preferences, as well as notifications on our platform, for information about their sessions, questionnaires to complete, and any updates from the therapist and research team. Weekly sessions will be scheduled collaboratively with participants with flexibility incorporated into the available hours, and with the scheduling and rescheduling of sessions as needed. This flexibility will ensure therapists can identify and address any relevant barriers to a participant’s involvement. If a participant misses two sessions without further follow-ups with the research team, they will be invited to reconsider a better time to join the project. Further, participants will be paid for each session and packet of measures completed. For instance, within a pilot study of the HRTP trial, participants received $5 for each session as well as $30 for each battery of measures completed (e.g., intake and week 4).

The approach and strategies of this study are specific to racialized communities recognizing the historical and contemporary barriers to research access and participation. Specifically, we recognize participants will need explicit information and engagement as many might not have prior experience of participating in a clinical treatment study. Additional effort and time will be taken to answer participant questions, explain the process of their participation, and flexibility will be built into the design to support their continued involvement. These methodological considerations are essential to working with racialized communities experiencing racial trauma and the design and implementation are deliberate to centre the concerns of these communities to ensure their equitable and inclusive participation.

As an additional equitable measure, upon completion of the TAU control arm and the 4-month follow-up, participants will be offered the opportunity to receive the HRTP treatment arm independent of their trial participation.

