Moreover, the research team will use targeted emails, social media posts, local bus ads, and word of mouth to advertise the study, instructing interested individuals to reach out to a study-specific email address. Once interest is confirmed, an email response will be sent with detailed information about the study and a consent form for consideration. The said study-specific email address will also present a direct contact with whom prospective participants may communicate should they have any questions or concerns about the study. Those interested in moving forward will be invited to partake in a 3 h virtual intake session (See Table 1 for the participants’ assessment schedule). During this intake, a trained research assistant will (i) describe important elements of the study, including the participant’s role and responsibilities; (ii) collect the necessary information from the participant to start a “file” (e.g., date of birth, gender, occupation, ethnoracial identity, contact information, emergency contact); (iii) and administer two semi-structured diagnostic interviews (i.e., the Mini International Neuropsychiatric Interview as well as the University of Connecticut Racial/Ethnic Stress & Trauma Survey). A 15 min break will be provided at the halfway point of the intake session. Using this intake information, the research team will continually and iteratively assess the demographic characteristics of the enrolled participants, gender and otherwise, to ensure sample heterogeneity and the generalizability of the findings (e.g., age, ethnicity, immigrant status, and socioeconomic status). Participant personal information and identifiers will be stored in a data management system to ensure participant privacy protection and data security. Data used for analysis will only include unique identification numbers assigned to each participant at intake. The data will be published in aggregate form and no participant identifier will be included.

Following intake, the participants will be randomly assigned to one of two groups: the HRTP (intervention) group or the control group (TAU). The randomization will be conducted using a computer-generated randomization sequence with stratification by age, gender, and the baseline level of racial stress (via the Racial Trauma Scale; Williams et al., 2022b).

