### 2.9. Primary Outcomes

Three primary outcomes will be measured at five time points for the treatment group (weeks 0, 4, 8, 12, and 28) and twice for the TAU control group (weeks 0 and 12). See Table 1 for the participants’ assessment schedule. Of note, there will be a differential assessment schedule for TAU versus HRTP participants. That is, HRTP participants are assessed on three more occasions than those in the TAU group. Two of these additional assessment periods are included within the intervention arm’s active treatment phase (weeks 4 and 8) to better understand how each HRTP phase impacts healing/racial trauma symptom severity. Week 4 roughly translates to the participants transitioning to the Healing phase and week 8 the Empowerment phase. Further, those in the control arm have no need for a post-treatment follow-up as upon receiving TAU, they may be immediately enrolled within the treatment group to receive the HRTP.

The *Racial Trauma Scale* (RTS; Williams et al., 2022c) is a 30-item clinical measure which examines the severity of traumatic symptoms due to racism. More specifically, the RTS asks individuals to “think about all the times when you have heard about, seen, or experienced racial discrimination” and how much they have been bothered by resultant thoughts, behaviours, or symptoms on a 4-point scale (where 1 is “not at all” and 4 is “extremely”). Of note, within this study specifically, when completing the RTS, clients will be asked to rate symptoms as per their lived experience over the previous month/30 days. An RTS total score is calculated by summing all item ratings together. Moreover, subfactors of the RTS include “Lack of Safety”, “Negative Cognitions”, and “Difficulty Coping”. Higher RTS total and subfactor scores indicate greater symptom distress. In consideration of the RTS’s convergent validity, RTS responses were found to be highly correlated with several measures of trauma, including the *PTSD Checklist for the DSM-5* (PCL-5; r = 0.79) and the *General Ethnic Discrimination Scale* (r = 0.76). The RTS was developed for and tested with diverse ethnoracial populations. The RTS also has excellent reliability (α = 0.97; Williams et al., 2022c).

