### 2.12. Statistical Analysis

Descriptive statistics, including means, standard deviations, and frequencies, will be calculated for continuous primary and secondary outcomes. Differences in primary and secondary outcomes, including TSDS, RTS, change in symptoms, and therapeutic experiences, will be examined using a two-way mixed ANOVA with two or three within-subject levels of time (pre-test, post-test, and follow-up) and two between-subject levels of condition (HRTP and control). When there is evidence of sphericity violation, we will use the Greenhouse–Geisser correction (Greenhouse & Geisser, 1959). It is predicted that participants’ TSDS and RTS scores will decrease significantly over the course of the treatment. It is also predicted that TSDS and RTS scores at follow-up will be the same or lower than at the end of the treatment.

Both the short-term and long-term efficacy of the HRTP will be examined during the treatment (week 0, 4, 8), at the end of the treatment (week 12), and 4 months after the treatment (week 28). Assessment will take place at four time points for the treatment group (HRTP therapy; weeks 0, 4, 8, 12, and 28; see Table 1 for participants’ assessment schedule) and only two time points for the control TAU group (T0 and T4; see Table 1 for participants’ assessment schedule). Analysis will compare standard mean differences (SMDs) between the time points for the treatment group (weeks 0, 12, and 28) and the control group (weeks 0 and 12). Analyses will entail intent to treat (ITT) and include participants with pre-treatment and the last time point available as long as they attended at least one treatment session. We examine significant levels for the analysis as well as effect sizes. A significance level of *p* < 0.05 will be used for all tests.

For each outcome of interest, we will identify any significant Condition × Time interactions. When no interaction is found, significant main effects will be reported. Partial eta-squared (η2) was used to measure effect sizes for the ANOVAs. When significant interactions are found, post hoc tests of simple main effects will be used to examine the differences, *p* values will be included for all post hoc tests, and 95% confidence intervals (CIs) will be used for all *p* values less than 0.05. Additionally, we will conduct comparisons of baseline data for completers and non-completers. Subgroup analysis will be based on age, gender, and levels of racial stress and trauma.

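### Section 2.4 treats randomised participants who miss two sessions as not yet in the trial, which leaves their follow-up and allocation unsettled and does not fit the intention-to-treat label in 2.12

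*Protocol article*

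**What the plan says.** Section 2.3 of the protocol article places randomisation after intake: "Following intake, the participants will be randomly assigned to one of two groups". Section 2.4 gives the same order: "Once participants have completed the intake process and are fully onboarded, they will be assigned to a treatment group and a therapist". Section 2.4 then states the rule on missed sessions. Of a participant who misses two of them and has had no further follow-up with the team, it says that "they will be invited to reconsider a better time to join the project". It does not say whether the person is withdrawn, whether later questionnaires are still sent, or which baseline and allocation apply on return. It does provide for questionnaire reminders, and it pays for each set of measures as well as for each session.

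Section 2.12 calls the analysis intention-to-treat and says that the analyses "include participants with pre-treatment and the last time point available as long as they attended at least one treatment session". For those who do not complete, the only other planned step concerns baseline: "we will conduct comparisons of baseline data for completers and non-completers".

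Section 2.9 sets different schedules by arm. The primary outcomes are taken in HRTP at weeks 0, 4, 8, 12 and 28, but in TAU only at weeks 0 and 12. Table 1 agrees and shows no TAU measures at weeks 4 and 8.

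**The concern.** Intention-to-treat needs every randomised person to be followed as far as possible and analysed in the allocated arm. A rule that acts after randomisation, is triggered by attendance, and speaks of joining the project points the other way. Attendance can depend both on the treatment received and on how the person is doing, so loss linked to it need not be balanced between arms.

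Two things are at stake. The first is the week-12 comparison of HRTP with TAU. If non-attenders provide no week-12 value, the plan falls back on the last time point available, and what is available differs by arm. The second is the identity of a returning participant. If that person counts as a new joiner, it is unclear which baseline and which allocation the analysis should use.

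**Working it through.** The plan gives no figure on this point to reproduce, so the check is mainly a comparison of its statements.

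**Step 1: order of events.** Sections 2.3 and 2.4 agree: intake, then random assignment, then sessions. Anyone who has missed two sessions is already randomised. An invitation to join at another time is therefore addressed to someone who, under intention-to-treat, is already in.

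**Step 2: what 2.12 does with such a person.** The table combines the one-session condition in 2.12 with the schedules in 2.9 and Table 1. Rows two to four assume that no measure is collected after the person leaves.

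| Situation | HRTP | TAU |
|---|---|---|
| Attends no session | Excluded by 2.12 | Excluded by 2.12 |
| Attends, leaves before week 4 | Baseline only | Baseline only |
| Attends, leaves between weeks 4 and 8 | Week 4 value | Baseline only |
| Attends, leaves between weeks 8 and 12 | Week 8 value | Baseline only |
| Stops sessions, completes week 12 | Week 12 value | Week 12 value |

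The arms are handled differently in rows three and four. Where only baseline exists, 2.12 does not say whether the person is dropped or counted as unchanged. The last row is the only one that gives each arm the outcome it needs, and 2.4 leaves open whether it will happen.

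**Step 3: how many people could be affected.** Section 2.2 plans for 20% attrition with 48 per group: 0.20 × 48 = 9.6, about 10 per arm. In the pilot (section 2.11), 4 of 14 clients left early: 4/14 = 28.6%, and 48 × 4/14 = 13.7, about 14 per arm at that rate. These counts cover loss of every kind. The documents do not say what part would fall under the two-session rule.

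**Step 4: illustration of bias, on assumed inputs.** Suppose a share p of HRTP and q of TAU have no week-12 value, and in both arms leavers differ from stayers by g SD in the true outcome. The mean of stayers in an arm then differs from the mean of all randomised by (share lost) × g. The between-arm contrast in stayers is therefore off by (p − q) × g.

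- p = 0.286, q = 0.10, g = 0.2: 0.186 × 0.2 = 0.037 SD.
- p = 0.286, q = 0.10, g = 0.5: 0.186 × 0.5 = 0.093 SD.
- p = q, same g in both arms: 0.

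Only the 0.286 comes from the documents, and it comes from a pilot without a control arm. The values of q and g are assumptions. The formula also describes an analysis of observed week-12 values. Under the last-available rule the error further depends on how far a week 4 or 8 value lies from the unobserved week-12 value, and on how baseline-only TAU participants are counted. The documents give neither.

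**The case against.** The strongest reply is that the sentence in 2.4 is an outreach offer in a section about retention. It is an invitation, not a withdrawal. It applies only to people who have missed two sessions and have had no further follow-up with the team, so it may describe people already being lost and not cause the loss. A reader might infer that the rule removes non-attenders from outcome collection, but the article does not say so. Payment for measures is listed alongside payment for sessions, and nothing makes it depend on attendance. All of this stands.

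A reader might also infer that the groups compared become those who kept attending. That goes too far: 2.12 keeps anyone who attended once and has a later measure. Nor does any text say that returners are randomised again or counted twice. Section 2.3 assigns a unique identification number at intake, which points against double counting.

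It is also fair to say that the most explicit departure from intention-to-treat is the one-session condition in 2.12, and that the uneven data on leavers come from the schedules in 2.9. Both would remain if the sentence in 2.4 were deleted.

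The claim that nothing more than condensed detail is missing does not stand. The article states a post-randomisation rule in words that treat a randomised person as outside the trial, and elsewhere it states intention-to-treat. Those two statements need to be reconciled whatever the full protocol adds.

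**Conclusion.** The point holds as an unresolved conflict between 2.4 and 2.12, made more consequential by the unequal assessment schedules. It is worth correcting before recruitment, because the remedy is cheap and week-12 data not collected from leavers cannot be recovered by analysis.

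Its size cannot be derived from the documents. Under the assumptions in the working, an analysis of observed values would be off by about 0.04 to 0.09 SD, and by nothing if loss and leavers are alike in both arms.

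A reader might be tempted by a larger figure. If the pilot's 4 of 14 gained nothing over TAU and the rest gained 0.52, the effect in all randomised would be 0.52 × (1 − 4/14) = 0.371, so stayers would overstate it by 0.52 − 0.371 = 0.149 SD, or 40% (0.52/0.371 = 1.40). The documents do not support using this as the bias of the trial. It describes a stayers-only analysis that 2.12 does not plan, it takes 0.52 as the effect in stayers where section 2.2 gives it as the difference between groups, and it assumes no benefit at all in leavers.

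**What to change.** In 2.4, separate stopping sessions from leaving the study. State that every randomised participant who has not withdrawn consent is sent the scheduled week-12 RTS, TSDS and BDI-II, and the week-28 set where it is scheduled, whatever their attendance. State that a returning participant keeps the original identifier, baseline and allocation and is not randomised again.

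In 2.12, analyse all randomised participants in the allocated arm and remove the one-session condition. With week-12 values sought from everyone, the end-of-treatment comparison relies less on earlier values that only HRTP has. The treatment of week-12 values that are still missing can be set out in the analysis plan.

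The cost is a change of wording, some extra reminders, and questionnaire payments to non-attenders for measures that are already scheduled. No position is taken on whether sessions should continue.

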### 2.5. Therapist Eligibility, Training, and Supervision

Given the innovative nature of the HRTP, extensive onboarding and training will be required to ensure therapists are competent and confident in terms of delivering the protocol. Given that many therapists may not have the necessary skills and training to work extensively with racialized communities, a selection, training, and supervision process was designed to supplement knowledge gaps in order to ensure therapists are comfortable discussing race and racism, can provide psychoeducation on race-based stressors, and possess the knowledge to address the racialized aspects of traumatic experiences (Carlson et al., 2018). *Therapists* are eligible for inclusion in this study if they are psychology doctoral students with at least one full year or more of advanced clinical training (i.e., practicum or internship level). Therapists will primarily be recruited through the authors’ host institution’s community mental health clinic. Note, at any given time within the year, approximately 50 doctoral students provide psychological services through the said clinic. Also of note, therapists within this study will be compensated for direct/participant-facing time accrued. That is, HRTP and TAU therapists alike will be paid for each completed session with a participant.

*Supervisors* are eligible for inclusion in this study if they (i) are licenced clinical psychologists and (ii) have previous experience supervising clinical trainees. Moreover, supervisors overseeing therapists within the TAU control arm of the study must be certified or experienced to work within the clinic delivering the TAU therapeutic sessions. Similarly, those supervisors supporting therapists within the HRTP intervention arm of the study must be experienced in working with real-world clients suffering from racial trauma. Whether supporting therapists within the HRTP or TAU arms of this study, supervisors will be paid for each hour spent in supervision.

*HRTP therapists* will partake in a multistep onboarding process before they are permitted to see clients. Moreover, depending on the therapists’ level of training and/or experience working with racialized clients, the onboarding process will be adapted to increase therapist comfort and efficacy.

As a first step of the onboarding process, interested parties will be required to respond to a standard set of questions (see Williams et al., 2022a for the full complement of questions). Sample questions from this set include:Have you had at least a one-semester graduate course (or the equivalent) focused on multicultural counselling skills? How have you applied it in your professional work?Are you willing to address racial differences with clients early in therapy? Give an example of how you would approach this.How would you respond if your client said you were a racist? Given that this question may require more context, assume that the client says this because you are either White or not the same race as they are.

Responses to the aforementioned questions will be used to gauge therapist interest, strengths, and gaps in training as well as to evaluate clarity, understanding of racism, and how it occurs in different settings. The Project Coordinator, and at least one other HRTP supervisor, will also review each submission against a study-specific rubric and follow up as needed on unclear elements or perceived gaps in responses. For instance, therapists may be assigned additional readings or role-play activities when their initial answers are insufficient.

In a second step, the therapists will be given mandatory material for review. Therapists with minimal clinical experience overall or in working with racialized clients will be required to read and reflect on two academic articles. Specifically, one article describing the character traits and behaviours of an anti-racist clinician (i.e., Williams et al., 2022a); and another describing the underlying mechanisms employed by the HRTP (i.e., Williams et al., 2023a). All HRTP therapists, regardless of experience level, must also watch three workshop videos recorded by the principal investigator, presenting each of the three phases of treatment in depth, with interactive case examples. To ensure therapists have thoroughly engaged with the material given, the therapists will prepare a short written or oral reflection on each article/video assigned. In so doing, the therapists will be asked to consider what they liked about the reading/video (and why), what they did NOT like about the reading/video (and why), and what impact the reading/video has on theory and practice. Again, the Project Coordinator and at least one other HRTP supervisor shall review the reflections, using another study-specific rubric, and provide commentary and guidance as needed.

Should the above two phases be completed smoothly and absent any issue, the therapists will be ready to be matched with a client. If the Project Coordinator and at least one other HRTP supervisor believe the individual requires extra support, a mock first session will be organized between the therapist and a peer. The Project Coordinator will provide feedback on the audio recording of said role play.

The *TAU therapists* will also partake in minimal onboarding activities including reviewing the trial protocol and an orientation at the control group’s treatment clinic, at the authors’ host institution. Onboarding for both HRTP and TAU therapists occurs before the said individuals see their first client. Nevertheless, training for both the intervention and control arms will not stop there. Once actively seeing clients, study therapists will be required to partake in weekly group supervision meetings. These meetings will last up to 90 min and be led by licenced clinical psychologists with general clinical experience (if a TAU supervision) or the HRTP (if an intervention supervision). Several supervision groups will run simultaneously to ensure group numbers remain low. That is, no more than 15 active therapists will be assigned to a single group supervision at a time. Moreover, while admission to supervision groups will be staggered (i.e., client and therapist onboarding-dependant), once placed, therapists will typically remain within their assigned group until they no longer wish to be part of the study (for case continuity and to more easily monitor therapists’ clinical goal progress).

